### Outcomes

#### Primary outcome: weight loss

Absolute (kg, BMI) changes and percent changes (%EWL, %TWL, % change in BMI) from baseline will be reported. Percent Excess Weight Loss (%EWL) is calculated as100% x ([W0 – W1]/EW0) where W0 is the weight (kg) at the time of the surgery, W1 is the weight (kg) at the last follow‐up and EW0 is the excess weight at the time of the surgery, based on ideal weights found in the Metropolitan tables for middle frame individuals [65]. Percent Total Weight Loss (%TWL) is calculated as 100 % x ([W0-W1]/W0) where W0 is the weight (kg) at the time of the surgery, W1 is the weight (kg) at the last follow‐up. Using definitions of successful weight loss 12 months after bariatric surgery, we will calculate the proportion of patients who attain (>50 % EWL). In addition, the proportion of subjects that achieve clinically important weight loss (i.e. ≥ 5 and 10 %) will be reported [3].

#### Sample size calculation

The primary outcome for the sample size determination was defined as successful weight loss at 12 months after bariatric surgery. This was calculated as percentage of patients who attain (>50 % EWL) at 12 months post-surgery. Sample size was estimated using an online calculator for population surveys as follows: *n* = (Z^2^ × P (1 – P))/E^2^ where Z = value from standard normal distribution corresponding to desired confidence level (Z = 1.28 for 80 % CI), P is expected true proportion and E is desired precision (half desired CI width). Assuming that 50–60 % of patients undergoing LSG will achieve the primary outcome of weight loss (>50 % EWL), a total of 165 patients will be required for a precision of ±5 % at a confidence level of 80 %. To account for missing information from some patients, the sample size has been inflated to 200.

#### Secondary outcomes

Complications of surgery30-day complication rate and mortality will be reported. Longer-term complications such as gastroesophageal reflux and micronutrient deficiencies will be examined. To examine micronutrient deficiencies, the following biochemical parameters associated with micronutrients will be assessed (25-hydroxyvitamin D (25-OH-D), parathyroid hormone (PTH), calcium, vitamin B12, ferritin, mean cell volume (MCV) and hemoglobin). The analysis for 25-OH-D used liquid chromatography coupled with tandem mass spectrometry. Hemoglobin and MCV were analyzed on the Beckman Coulter®HMX Hematology Analyzer, while ferritin, vitamin B12, and intact PTH were analyzed on the Architect i System by Abbots Diagnostics. Calcium was analyzed on the Architect c System by Abbots Diagnostics.Comorbid Condition Improvement/ResolutionImprovement in comorbid conditions (i.e. hypertension and dyslipidemia) is defined as any reduction in medication use or treatment. Comorbidity resolution is defined as complete cessation of treatment/medication.For the comorbid conditions of prediabetes and type 2 diabetes mellitus, specific definitions of diagnosis are used as outlined in the Canadian Diabetes Association Clinical Practice Guidelines [66]. Prediabetes is defined as fasting plasma glucose (FPG) levels of 6.1–6.9 mmol/L and/or glycated hemoglobin (A1C) levels of 6.0–6.4 % [66]. Type 2 diabetes mellitus is defined as FPG ≥ 7.0 mmol/L and/or A1C ≥ 6.5 % [66].Additional criteria will used to assess improvement and resolution of prediabetes and diabetes [67]. Case definitions of improvement and remission of prediabetes will be as follows: *Improvement* will be based on achievement of the following: (1) lower glycemic measures (2) at least 1 year’s duration, and (3) pharmacologic therapy required but at a lower dose. *Normalization* is defined as (1) normal glycemic measures (2) at least 1 year’s duration, and (3) pharmacologic therapy required but at a lower dose. *Remission* is based on (1) normal glycemic measures (2) at least 1 year’s duration, and (3) no active pharmacologic therapy. Case definitions of improvement and remission of Type 2 diabetes mellitus [67] will be defined as follows. *Improvement* will be based (1) hyperglycemia below diagnostic thresholds for T2DM (2) at least 1 year’s duration, and (3) pharmacologic therapy required but at a lower dose. *Partial remission* is based on the following (1) hyperglycemia below diagnostic thresholds for T2DM (2) at least 1 year’s duration, and (3) no active pharmacologic therapy. *Complete remission* is based on the following criteria (1) normal glycemic measures (2) at least 1 year’s duration, and (3) no active pharmacologic therapy.The status of specific biochemical parameters associated with NAFLD prior to and following LSG will be assessed using the following markers: total bilirubin, alanine phosphatase (ALP), alanine transaminase (ALT), gamma glutamyl transpeptidase (GGT), high-density lipoprotein (HDL), low-density lipoprotein (LDL), and triglycerides. Biochemical parameters associated with NAFLD were analyzed on the Architect c System by Abbots Diagnostics.The prevalence of PCOS will be determined prior to surgery based on self-report while changes in related (e.g., period frequency and regularity, menstrual flow and intensity, hirsutism, acne, fertility, post-surgery conception) and metabolic symptoms (insulin sensitivity, T2DM, dyslipidemia, hypertension) will be examined 1-year after LSG.Change in medication useChanges in prescription and over-the-counter medication use and associated costs will be examined including total number of medications and changes (dose changes, medication discontinuations, and initiation of additional medications) by disease indication.Quality of LifeHealth related quality of life is assessed using validated instruments. Generic and disease-specific instruments will be used. All participants will complete the Short Form (SF)-12, Euroqol (EQ)-5D, and the Impact of Weight on Quality of Life (IWQOL)-Lite pre-surgery at 6, 12, 18, and 24 months after surgery. The SF-12 (Version 2) is a condensed 12-question version of the SF-36 [68]. It yields a physical and a mental health component summary score. Three-to-five point difference in either score are considered clinically meaningful [69, 70]. The EQ-5D is an indirect preference-based health survey that consists of a 5 dimension descriptive system [71] and an overall health visual analog scale (EQ- VAS). A 0.03 point difference in EQ-5D index score and 10 point difference on the EQ-VAS are considered clinically meaningful [72]. The IWQOL-Lite is a short form of the IWQOL and is the first instrument specifically developed to assess the effects of obesity on the quality of life of persons who are seeking weight loss treatment [73]. The IWQOL-lite consists of 31 items that describe 5 domains of obesity-specific HRQL. A difference in the total score of 7–12 points for IWQOL-Lite is considered clinically meaningful [74].Economic consequences of bariatric surgeryDirect healthcare use/costs (e.g., hospitalizations, physician visits, medication use) and indirect costs (e.g., cost of weight loss interventions, employment and absenteeism, home productivity, transfer payments) will be compared 3 years prior to surgery and 2 years post- surgery in order to determine the economic consequences of bariatric surgery.

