#### The Newfoundland and Labrador Bariatric Surgery Cohort (BaSCo) study

##### Study objective

The objective of the current study is to examine short- to mid-term outcomes (2–4 years) associated with LSG. Eligible patients who have undergone LSG will be followed during and after surgery to assess health and other outcomes. Specific study objectives are to examine:30-day complication rate and mortality, and long-term complications (e.g., gastroesophageal reflux, micronutrient deficiencies).reduction in weight and/or body mass index (BMI), including predictors of successful weight loss.improvement or resolution of co‐morbid conditions (i.e. diabetes, hypertension, dyslipidemia, NAFLD, PCOS).changes in prescription and over-the-counter medication use.improvement in measures of health‐related quality of life andthe economic consequences associated with LSG (e.g., direct costs and indirect costs).

In the short- to mid-term we hypothesize a low rate of complications, a marked reduction in weight, improvement/resolution of comorbid conditions, a reduction in obesity-related medications, an improvement in quality of life, and a decrease in direct healthcare and indirect costs compared to pre-surgery costs.

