
### Data analysis

Non-identifying patient information obtained from the standardized case report forms used to collect patient information at baseline, administrative records and medical chart reviews were entered into a Statistical Package for Social Sciences database. All statistical analyses will be performed using IBM SPSS Statistics for Windows, version 20.0 [75]. Descriptive analysis will include demographic details of patients pre-surgery and clinical information collected at the time of surgery. In each analysis to be conducted to address the six main research objectives for this program, categorical variables (such as 30-day complication rate and mortality; and long-term complications e.g., gastro esophageal reflux, micronutrient deficiencies) will be presented as frequencies and chi-square tests conducted to identify differences in pre–post surgical outcomes. Continuous variables with a normal distribution will be reported as means ± SD. Variables with a non-normal distribution will be reported as medians and interquartile ranges. For example, health services use such as number of physician visits often has a non‐normal distribution; therefore median and quartiles will be reported when comparing use pre‐ and post‐surgery. The Analysis of Variance (ANOVA) or the paired t-method will be used to assess differences in continuous outcome pre and post-surgery. Pairwise-comparison of pre with post-surgical patients’ outcomes at 3, 6, 12, 18 and 24 months will be done using matched t-tests for continuous outcomes such as BMI. Regression analyses methods will be performed to identify independent predictors of outcomes of interest (i.e., reduction in weight and/or BMI, including predictors of successful weight loss; improvement or resolution of co‐morbid conditions (i.e., diabetes, hypertension, dyslipidemia, NAFLD, PCOS); changes in prescription and over-the-counter medication use; improvement in measures of health‐related quality of life. For continues outcomes, mean differences, standard errors, 95 % confidence intervals and p-values will be presented. For categorical outcomes, odds ratios and 95 % confidence intervals will be presented. Generalized estimating equations with binary logistic regression will be used for all response or outcome events to take into account the correlations between repeated measures post-surgery providing an estimated adjusted odds ratio and 95 % confidence intervals. Statistical significance is set at *p* < 0.05.

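### Improvement in hypertension and dyslipidemia counts only medication reductions, has no worsened category, and is zero before surgery, so a pre-post test on it would not test net change

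*Protocol article*

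**What the plan says.** The third study objective is "improvement or resolution of co‐morbid conditions (i.e. diabetes, hypertension, dyslipidemia, NAFLD, PCOS"), and the study hypothesis includes improvement or resolution of these conditions.

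Under Secondary outcomes, improvement in comorbid conditions is given for two of them: "hypertension and dyslipidemia) is defined as any reduction in medication use or treatment". The next sentence reads "Comorbidity resolution is defined as complete cessation of treatment/medication". No worsened state is defined, and no rule says how a reduction in one drug is set against an addition or increase in another. The type 2 diabetes rule is stricter; its improvement category needs "hyperglycemia below diagnostic thresholds for T2DM (2) at least 1 year’s duration, and (3) pharmacologic therapy required but at a lower dose".

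A separate medication-use outcome does look both ways: it covers "dose changes, medication discontinuations, and initiation of additional medications) by disease indication".

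The Data analysis section opens its testing plan with a general sentence: "In each analysis to be conducted to address the six main research objectives for this program, categorical variables", followed by examples, "will be presented as frequencies and chi-square tests conducted to identify differences in pre–post surgical outcomes". Significance is set at p < 0.05. The same section names improvement or resolution as an outcome for predictor regressions, and plans generalized estimating equations for repeated post-surgery measures.

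**The concern.** The flag records reductions and nothing else. Under ordinary prescribing some patients will have a drug or dose reduced and others will have one added or increased, whether or not surgery does anything. The first group adds to the improvement proportion and the second never subtracts from it. The article describes no control group that would remove this background.

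The flag also has no free pre-surgery value: nobody can have reduced from baseline at baseline. A pre-post test on it would ask whether anyone had a reduction, not whether reductions outnumber increases. An ordinary chi-square would also treat the two measurements on each patient as independent groups.

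At stake is the third objective for two conditions that each affect about half the cohort. The improvement proportion, and any p-value attached to it, would lean towards the study's hypothesis. The same flag would serve as an outcome in the predictor models.

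**Working it through.** The article states no figure for this outcome, so there is none to reproduce. The check asks how few reductions make a pre-post test significant, and how often chance alone would supply them.

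**Inputs from the article**
- Sample size 200, inflated from 165 (Sample size calculation).
- Prevalence of hypertension and dyslipidemia about 50% (Discussion). This gives 0.50 × 200 = 100 affected patients per condition, or about 82 if only 165 are evaluable.
- Significance level 0.05; two-sided is assumed.

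**Assumptions not in the article**
- All affected patients are on drug treatment.
- Surgery has no effect.
- A share t has a chance reduction and an equal share t a chance increase. The range shown is t = 1% to 10%.

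**Step 1: threshold for significance.** Compare 0/100 before surgery with k/100 after.
- Uncorrected chi-square = 200 × (100k)² / (100 × 100 × k × (200 − k)). For k = 3 this is 3.05; for k = 4 it is 4.08. The critical value is 3.84, so 4 patients suffice.
- Exact McNemar with all discordance one way: p = 2 × 0.5^k. For k = 5, p = 0.0625; for k = 6, p = 0.031. So 6 patients are needed. Continuity-corrected chi-square and Fisher's exact test also need 6.

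The thresholds are the same for 82 patients.

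**Step 2: chance of reaching it with no effect.** P(X ≥ 4) or P(X ≥ 6), with X binomial (n, t):

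| t | n = 100, chi-square | n = 100, exact McNemar | n = 82, chi-square | n = 82, exact McNemar |
|---|---|---|---|---|
| 1% | 0.018 | 0.001 | 0.009 | 0.000 |
| 2% | 0.141 | 0.015 | 0.082 | 0.006 |
| 3% | 0.353 | 0.081 | 0.232 | 0.037 |
| 5% | 0.742 | 0.384 | 0.591 | 0.227 |
| 8% | 0.963 | 0.820 | 0.902 | 0.649 |
| 10% | 0.992 | 0.942 | 0.969 | 0.841 |

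Pairing alone does not cure the problem. The McNemar columns are lower but still climb towards 1, because the comparison is still with a structural zero.

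**Step 3: two-way comparison.** Count increases as worsening and apply an exact sign test to improved versus worsened, with t = 5% to 20% each way and n = 100. It falsely favours improvement in 1.1-1.7% of trials and rejects in either direction in 2.2-3.5%, below the nominal 5% at every rate tried.

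**The case against.** Several points on the other side are sound.

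- **The test is inferred.** A reader might take the plan to commit itself to a pre-post chi-square on the improvement flag. It does not say so. The general sentence covers all six objectives, but its examples are complications, mortality, reflux and deficiencies, and 30-day complications and mortality have no pre-surgery value either. Where the section names comorbidity improvement, it assigns regression. A pre-post test of treated status would not start from zero, although it would not test improvement as defined.
- **The turnover rate is unknown.** A reader might infer that ordinary prescribing turnover would by itself produce a significant result. At 1-2% it seldom would. The result is conditional on t and on the share treated, and the article gives neither.
- **Relapse is not hidden.** A patient back on baseline treatment at a later visit is no longer reduced, so the proportion falls. Step-ups beyond baseline are reported by indication under medication use.
- **A drug swap is ambiguous.** Dropping one drug and starting another counts as improved on one reading of the definition. Another reading is that medication use has not been reduced.
- **Resolution is unaffected.** Complete cessation cannot coexist with an added drug for the same condition.
- **A large effect would dominate.** The review summarised in the Background reports remission of 68-76% for these two conditions. At that size a few percent of turnover would not decide whether an effect exists.

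These points limit the claim without removing it. The stated definition remains one-directional, its proportion still contains background reductions, and medication increases are kept out of the comorbidity conclusion.

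**Conclusion.** The point holds in a conditional form. The definition counts reductions only and has no worsened category, so the improvement proportion for hypertension and dyslipidemia includes whatever background reduction exists. If the general pre-post chi-square is applied to the flag, it compares with a structural zero and ignores pairing.

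With about 100 treated patients and balanced turnover, the false-positive rate runs from negligible at 1% to near certainty at 10%, and around 5% it depends heavily on the test chosen. This rests on the assumed turnover, on all affected patients being treated, and on the general sentence being applied to this flag. The documents do not support saying that turnover will produce a positive result, or that worsening goes unrecorded. This is a secondary outcome, but it is a named objective and hypothesis, and the correction is cheap.

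**What to change.** Table 1 already records medication name, type, dosage, frequency and duration before surgery, at 3, 6, 12, 18 and 24 months, and annually after that. From these data, classify each patient with the condition at baseline, by indication and visit, as:

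- improved: a reduction with no addition or dose increase;
- worsened: an addition or dose increase with no reduction;
- unchanged/mixed: neither, or both.

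Report all three proportions at each visit, with the number on treatment at baseline beside them, because an untreated patient can move only towards worsened. Keep resolution as defined. Replace any pre-post chi-square on the improvement flag with an exact paired (sign/McNemar) test of improved versus worsened, and give the difference in proportions with a 95% CI.

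No new data are needed. The cost is one classification rule and a somewhat lower reported improvement proportion, since mixed changes no longer count. Without a control group, a general drift in prescribing would still be indistinguishable from an effect of surgery; the change removes only the one-way counting.

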## Discussion

In summary, the demand for LSG as a stand-alone procedure is growing in popularity as a treatment for class II and III obesity. In a joint report “Developing a Research Agenda to Support Bariatric Care” published by the CIHR and the Canadian Obesity Network in 2010, the gaps in research related to bariatric surgery were highlighted [78]. Although LSG was not specifically highlighted in the report, compared to other bariatric surgeries, research on LSG as a treatment for severe obesity is limited due to its relatively recent provision as a stand-alone procedure. The start-up of a bariatric surgery program offering LSG as a treatment for severe obesity combined with the limited research on LSG provided an opportunity for research. Consequently, an Integrated Knowledge Translation Team was established at Memorial University, comprised of academic researchers, healthcare professionals, decision-makers, and policy makers, and a program of research on bariatric care was developed to address key gaps in the research literature. One of the studies designed and implemented within this program of research and presented in this paper is a quasi-experimental study that aims to address current knowledge gaps in LSG by generating prospective, population-based Canadian outcome data. This study is being conducted in a provincial bariatric surgery program within a tertiary care teaching centre and the results will be generalizable to similar programs offering bariatric surgery. A current review continues to highlight a major concern previously identified by others [79, 80] associated with bariatric surgery as a treatment for obesity. It is not the magnitude of initial weight loss which has been well documented but the mid- to long-term sustainability of weight loss that is under question. Very few bariatric studies report long-term results with sufficient patient follow-up (>80 %) in order to minimize biased results. In addition, insufficient evidence exists regarding long-term outcomes for LSG [61]. In response to this concern and as part of the current study protocol, a clinical database to house all program data in order to monitor longer-term (>5 years) patient health outcomes has been developed which will also allow for data linkages with administrative data to examine health care use and costs in the future. Further interventions being used in order to decrease attrition and increase patient engagement include the use of technology (e.g., Tele-health and webinar sessions for educational purposes). As of August 2015, 100 % recruitment has been achieved with completion of follow-up to be completed by September 2016 with study results to be published in late 2016 and early 2017. Our study population is 82 % female, with an average age, weight, and BMI of 44 years, 135 kgs and 49 kg/m^2^, respectively. The prevalence rates of hypertension and dyslipidemia were approximately 50 and 43 % had T2DM. Our study participants are similar to other patient populations that are eligible for and undergoing bariatric surgery elsewhere in Canada [15, 21], increasing the external validity of our study findings.

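### Pregnancy is excluded only at entry, so weights, laboratory values and drug stops during a later pregnancy are scored at face value by the weight-loss, hypertension, dyslipidemia, NAFLD and micronutrient definitions

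*Protocol article*

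**What the plan says.** All places are in the protocol article.

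- **Exclusion criteria**: pregnancy is the sole entry, with no rule for pregnancy after enrolment. **Inclusion criteria** admit ages 19 to 70. The **Discussion** reports that "Our study population is 82 % female" with a mean age of 44 years.
- **Secondary outcomes**, PCOS paragraph: changes in related features are examined one year after surgery ("e.g., period frequency and regularity, menstrual flow and intensity, hirsutism, acne, fertility, post-surgery conception"). Table 1 limits the PCOS assessment to 12 months.
- **Primary outcome: weight loss**: in both %EWL and %TWL, "W1 is the weight (kg) at the last follow"-up, with no exception.
- **Secondary outcomes**, comorbidities: improvement of hypertension and dyslipidemia "is defined as any reduction in medication use or treatment", and "Comorbidity resolution is defined as complete cessation of treatment/medication". Neither refers to a blood pressure or lipid value, or to the reason for the change.
- The diabetes categories are stricter. Complete remission, for example, needs "(1) normal glycemic measures (2) at least 1 year’s duration, and (3) no active pharmacologic therapy".
- **Secondary outcomes**, NAFLD: "The status of specific biochemical parameters associated with NAFLD prior to and following LSG will be assessed" through bilirubin, ALP, ALT, GGT and lipids. Ferritin, hemoglobin and MCV are among the micronutrient markers.
- **Table 1**: weight, laboratory values and medication are collected at 3, 6, 12, 18 and 24 months and annually. Pregnancy status is not among the listed variables.
- **Data analysis**: no rule defers, flags or sets aside visits during or soon after pregnancy.

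**The concern.** The protocol foresees an event that makes some of its measurements uninterpretable for their stated purpose, and then fixes definitions that score those measurements as they stand. Gestational weight would count as poor loss or regain. A drug stopped because of pregnancy would count as resolution of hypertension or dyslipidemia. Laboratory values that pregnancy itself can shift would be read as a nutritional or hepatic effect of surgery.

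The first two errors push in opposite directions: apparent weight loss falls while apparent comorbidity resolution rises. They fall only on women of child-bearing age, so they do not average out across the cohort. Any analysis restricted to younger women or to women with PCOS would carry a greater share of them. The one item that records conception sits in the PCOS assessment at month 12. That item would miss pregnancies in women without PCOS and conceptions after month 12.

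**Working it through.** **1. The plan's own figure.** The sample size formula is n = Z²·P(1−P)/E². With P = 0.50 and E = 0.05, Z = 1.28 gives 163.84 (164) and Z = 1.2816 gives about 164.2 (165). The stated 165 is reproduced. The benchmark for size is therefore ±5 points at 80 % confidence. The sample size is not in dispute.

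**2. Effect on one woman.**
- Inputs from the Discussion: mean weight 135 kg, mean BMI 49.
- Height = √(135/49) = 1.66 m.
- Assumed ideal weight at BMI 25 (the Metropolitan table values are not in the article): 25 × 135/49 = 68.9 kg. Excess weight = 135 − 68.9 = 66.1 kg.
- Assumed pregnancy weight of 10 kg: 10/66.1 = 15.1 points of %EWL. With 5 kg it is 7.6 points, and with 15 kg it is 22.7 points.
- The Background cites an average of 56.1 % EWL within the first year. 56.1 − 15.1 = 41.0, so an average patient would move from success to failure.

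**3. Number of women affected (assumed, since no rate is given).**
- Women: 0.82 × 200 = 164.
- 30–40 % of child-bearing potential: 49 to 66 women.
- 5–10 % of those pregnant or recently delivered at a given 12 to 24 month visit: 49.2 × 0.05 = 2.5 to 65.6 × 0.10 = 6.6, so about 2 to 7.

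**4. Effect on the success proportion.**
- Ceiling, if every affected woman changed category: 2.5/200 = 1.2 points to 6.6/200 = 3.3 points.
- Only women otherwise between about 50 and 65 % EWL can cross the line. Take P = 0.50–0.60 (the plan's figure), a normal distribution of %EWL, and an assumed SD of 15–25 points, so that the mean is 50 + SD·Φ⁻¹(P). The share in that band is then 23 % (P = 0.50, SD 25) to 37 % (P = 0.60, SD 15).
- Women who change category: 2.5 × 0.23 = 0.6 to 6.6 × 0.37 = 2.4. Over 200 patients that is 0.3 to 1.2 points.

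**5. Wider range, for a reader who doubts step 3.**

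| Share of all 164 women pregnant at 12 months | Women | Ceiling (points) | With 23–37 % crossing (points) |
|---|---|---|---|
| 1 % | 1.6 | 0.8 | 0.2–0.3 |
| 2 % | 3.3 | 1.6 | 0.4–0.6 |
| 5 % | 8.2 | 4.1 | 0.9–1.5 |
| 10 % | 16.4 | 8.2 | 1.9–3.0 |

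The last row would require 25–33 % of the women of child-bearing potential to be pregnant at once (10/40 to 10/30), which is hard to credit at a mean age of 44. Over the whole table, with 5–15 kg of pregnancy weight, mean %TWL moves by 0.03 to 0.91 points.

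**6. Medication and laboratory outcomes.** No arithmetic is possible, because the documents give neither a pregnancy rate nor a rate of pregnancy-driven drug changes. The logic is enough. A woman on one antihypertensive who stops it because she is pregnant meets the resolution definition at that visit. A woman with diabetes who stops treatment does not enter any remission category unless glycemic targets are also met and at least one year has passed.

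**The case against.** The strongest case against runs as follows. Only a condensed article is shown. Handling of pregnancy visits could sit in the full protocol, the analysis plan or the case report forms, and excluding pregnant patients at entry is compatible with recording conception later. This stands in part: the article cannot show that pregnancy status goes unrecorded, and a rule may exist elsewhere. It does not dispose of the point, because the article itself fixes the follow-up weight and the medication definitions, and as worded these give a wrong value for the affected visits.

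Four stronger readings are tempting, and the documents do not support them.

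- *Conception is a planned endpoint.* It is one example item in the PCOS assessment at 12 months.
- *Diabetes remission is contaminated in the same way.* The glycemic and one-year conditions largely prevent that.
- *Age, sex and PCOS predictors are distorted.* The Data analysis section speaks only of baseline patient factors and names none, so this is an inference.
- *The success proportion shifts by 1 to 3 points.* That needs every affected woman to cross the 50 % line, and counts recently delivered women as still carrying the full gain.

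It can also be argued that an effectiveness cohort should analyse everything observed, and that removing data after a post-surgery event that surgery may itself influence can introduce selection. That is fair. It is a reason for reporting both analyses, but not for leaving the rule unstated. Finally, the absence of a blood pressure or lipid value from the resolution definition is a wider weakness, of which pregnancy is one instance.

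**Conclusion.** The point holds in a limited form. Follow-up weight, and the improvement and resolution definitions for hypertension and dyslipidemia, take pregnancy-time data at face value. Pregnancy-time laboratory values also enter the NAFLD and micronutrient comparisons. Prediabetes and diabetes are largely protected.

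For the proportion above 50 % EWL, the likely movement is about 1 point or less (0.3 to 1.2). This rests on an assumed 2 to 7 affected women, 10 kg of pregnancy weight, a BMI-25 ideal weight and a normal %EWL distribution. It is small beside ±5 points and does not threaten the primary result. A reader might infer a material bias in the headline weight-loss figure, but nothing in the documents supports that. For an individual woman the error is large, about 15 points of %EWL, so a few patients could matter in analyses of younger women, the PCOS subset or a single comorbidity. Those effects cannot be sized, because the subset sizes are not given. The change is worth making because it is cheap.

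**What to change.** 1. **Identify pregnancies in all women**, not only those with PCOS. Use one case report form item for visits still to come. The Discussion puts the end of follow-up at September 2016 with recruitment already complete, so visits already held need chart review or the linked inpatient and physician-billing data described under Evaluation of health care utilization and costs.
2. **Main analysis**: set weight, BMI and pregnancy-sensitive laboratory values to missing during pregnancy and for a postpartum window stated in advance.
3. **Comorbidities**: do not count medication reduced or stopped because of pregnancy as improvement or resolution.
4. **Denominator**: state it for the 12-month success proportion. The mixed model handles gaps only in the weight trajectory. It does not cover that proportion, the matched t-tests, the chi-square tests or the GEE models.
5. **Reporting**: give the number of visits removed, add a sensitivity analysis with all observed data, and keep conception as a reported item.

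The cost is one form item, some chart or linkage work and a short analysis rule. The sample size does not change. The downside is a few missing visits, possibly several in a row for one woman. With a window of, say, 6 months after delivery, about 15 months (9 + 6) are removed, so conception at month 10 would take out the 12, 18 and 24 month visits. The length of the window is for the study team to choose and justify.
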